### Assignment of interventions: blinding

#### Who will be blinded {17a}

Participant and care team blinding is not possible in this trial. Study team members collecting qualitative and survey data collection cannot be blinded to study allocation. The statistician will provide unblinded data to the DSMB. The adverse event adjudication team will be blinded to study allocation, though members will have access to the patient’s EHR where CP notes may or may not be present for a given patient. We will use a group nomenclature (group 1 and group 2) during data analysis. The data will be unblinded for appropriate interpretation before publication. Analysis of quantitative data will be performed at the close of the study.

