### Data collection and management

#### Plans for assessment and collection of outcomes {18a}

Participants randomized to CACP will have access to CP services ordered and overseen by the treating clinical team per the current standard of care. Thus, the clinical trial evaluates the CACP care delivery model rather than the clinical care that is provided to patients within it. Participants randomized to usual care will not have access to CP services and will continue with their care as planned by the treating clinician(s).

All participants will complete a baseline survey at the time of enrollment/consent and at 30 days. Participants randomized to CACP will also complete a survey after their last CP encounter. Paper copies of the baseline surveys will be completed at the time of enrollment or provided to the participant and returned by mail. In the CACP treatment arm, we will ask that baseline surveys be completed and returned before or during the first CP visit. In the usual care arm, for participants who did not complete their baseline survey at the time of enrollment, up to 3 reminder phone calls will be made by a member of the research team to participants who have not returned their survey by the end of week 1.

Participants randomized to the CACP treatment arm will also be asked to complete a survey after their last CP visit. This survey will be handed to the participant by the CP at their last visit with a pre-stamped envelope so it can be completely private and returned by mail or sealed and given to the CP for delivery. If participants need help completing the survey, the research team study coordinator will contact them by telephone and complete the survey with them. Patients in the intervention arm who are recruited and consent to participate in an interview will complete it by telephone with a trained member of the study team unaffiliated with intervention delivery. Interviews will be audio-recorded with permission and transcribed for analysis.

Patients in both arms will be asked to complete a paper survey at day 30, administered between days 30 and 40 (first attempt) and with all 3 contact attempts completed by day 90. If participants need help completing the survey, it can be done over the phone with the research team study coordinator.

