#### Adverse event reporting and harms {22}

The study team will monitor for AE in both groups including ED visits, unplanned hospitalizations, deaths, falls with injury, and medication errors. SAEs for this study are any events that result in death, are life-threatening or place the participant at immediate risk of death from the event as it occurred, result in an ED visit or hospitalization, or cause persistent or significant disability or incapacity. The study statistician will check for hospitalizations, ED visits, and deaths on a weekly basis. Additionally, study coordinators review patient charts over the course of the study volunteer period, ensuring all adverse events are properly reported to the IRB as required per protocol. AEs and SAEs will be tracked in an Excel adverse event tracking log by the study research coordinators. AE and SAE that occur will be reviewed by the adjudication committee, which is comprised of clinical experts in hospital medicine, emergency medicine, cardiology, primary care, and paramedicine. The principal investigator is not a member of the adjudication committee.

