The adjudication committee will assess the relationship of all AEs to the study intervention, based on temporal relationship and clinical judgment. The degree of certainty about causality will be graded using the categories below.Definitely related—There is clear evidence to suggest a causal relationship, and other possible contributing factors can be ruled out. The clinical event, including an abnormal laboratory test result, occurs in a plausible time relationship to study intervention administration and cannot be explained by concurrent disease or other drugs or chemicals. The response to the withdrawal of the study intervention (dechallenge) should be clinically plausible. The event must be pharmacologically or phenomenologically definitive, with the use of a satisfactory rechallenge procedure if necessary.Possibly related—There is some evidence to suggest a causal relationship. However, other factors may have contributed to the event (e.g., the participant’s clinical condition, other concomitant events). Although an AE may rate only as “possibly related” soon after discovery, it can be flagged as requiring more information and later be upgraded to “probably related” or “definitely related,” as appropriate.Not related—The AE is completely independent of study intervention, and/or evidence exists that the event is definitely related to another etiology. There must be an alternative, definitive etiology documented.

All AEs related to the intervention will be reviewed in duplicate by two members of the adjudication committee, and their severity will be graded using the following guidelines:Mild–events that require minimal or no treatment and do not interfere with the participant’s daily activities.Moderate—events that result in a low level of inconvenience or concern with therapeutic measures. Moderate events may cause some interference with functioning.Severe—events that interrupt a participant’s usual daily activity and may require systemic drug therapy or other treatment. Severe events are usually potentially life-threatening or incapacitating. Of note, the term “severe” does not necessarily equate with “serious.”

Disagreements in adjudication will be reviewed by a different member of the adjudication committee. Final adjudication results will be compiled by the study coordinator and used for analysis and DSMB reporting purposes.

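### Severity is graded only for adverse events judged related to the intervention, so the severity data are a selected subset that cannot be compared between arms

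*Protocol article*

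**What the plan says.** All of the relevant text is in the protocol article.

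- **Collection** (section {22}, on adverse events and harms) is planned for both arms: "The study team will monitor for AE in both groups including ED visits, unplanned hospitalizations, deaths, falls with injury, and medication errors".
- **Committee review** (same section): "AE and SAE that occur will be reviewed by the adjudication committee".
- **Relatedness** (same section): "The adjudication committee will assess the relationship of all AEs to the study intervention". The listed grades are definitely, possibly and not related. For the last of these, "There must be an alternative, definitive etiology documented".
- **Severity** (same section): "All AEs related to the intervention will be reviewed in duplicate by two members of the adjudication committee, and their severity will be graded", on a scale of mild, moderate and severe.
- **Use of the results** (same section): "Final adjudication results will be compiled by the study coordinator and used for analysis and DSMB reporting purposes".
- **Blinding** (Who will be blinded {17a}): "The adverse event adjudication team will be blinded to study allocation", although the section adds that adjudicators can open the health record, where paramedic notes may appear.
- **Exposure of the control arm** (Plans for assessment and collection of outcomes {18a}): "Participants randomized to usual care will not have access to CP services". The section on non-adherence and missing data {20c} says the same for the 30-day follow-up period.

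**The concern.** Collection, committee review and the relatedness judgement all cover both arms. Severity grading does not. It depends on a relatedness rating that, in substance, only an event in the intervention arm can earn, because the other arm is not offered the intervention.

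This matters because seriousness separates events poorly in this trial. Any event that results in an ED visit or hospitalization is an SAE, so SAE status alone does not tell a minor ED visit from a grave one. The article itself notes that severe and serious are different things. A severity grade is the natural way to describe events of the same type, and the DSMB would naturally want it by arm when reading an imbalance in SAEs. Under the stated rule, the grades it receives come mostly from one arm, and only from some of that arm's events.

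**Working it through.** No arithmetic applies. The point concerns which events receive a grade and does not depend on alpha, power, effect size, standard deviation or sample size. The check is to follow an event through the steps in section {22}.

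| Step | Intervention-arm events | Usual-care events |
|---|---|---|
| Monitored and logged | All | All |
| Seen by the committee | All | All |
| Relatedness judged | All | All |
| Duplicate review and severity grade | Those judged related | Those judged related |
| Used for analysis and DSMB reports | Graded subset | Graded subset |

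1. **Does the severity sentence cover all events?** No. Its subject is the events related to the intervention, and the severity to be graded is theirs. The sentence before it, on relatedness, covers all events, so the narrowing is explicit.

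2. **Does another section extend grading?** No. Table 1 lists safety outcomes by occurrence, count and time to event. The sections on blinding, interim analyses and the DSMB do not mention severity grades.

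3. **Can a usual-care event be judged related?** In substance hardly ever, since these participants are not given paramedic services. On paper it can happen. The adjudicators are blinded to allocation, and a rating of not related needs a documented definitive alternative cause. An event without one may be rated possibly related and then graded. This assumes that possibly related counts as related, which the article does not state. If it does not count, the graded subset is narrower still.

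4. **Are all intervention-arm events graded?** No. Those judged not related stop at the relatedness step.

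5. **Can the resulting grades be compared between arms?** No. In the intervention arm they describe events attributed to the program. In usual care they describe the few events for which a blinded adjudicator lacked a definitive alternative cause. The two sets are selected differently, so a difference in their severity mix would not estimate a difference between the arms.

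6. **Which planned results depend on the grades?** None of the named ones. The Table 1 safety outcomes use event occurrence. Both parts of the accrual-pause rule use participants with an SAE, by arm. What is affected is the severity part of the adjudication results that go to analysis and to the DSMB.

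**The case against.** The strongest reply is that nothing the article promises fails. It states no between-arm comparison of severity, and its safety outcomes and pause rule use data collected in both arms. This is correct, and it limits the weight of the point. It does not remove it, because the same section sends the adjudication results to analysis and to the DSMB.

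A second reply is that a condensed article leaves operating detail to a fuller document. That would answer a missing rule. Here the rule is stated, and it is the stated rule that selects the events.

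Four stronger readings are tempting, and the documents do not support them.

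- **No usual-care event can ever be graded.** A reader might infer this, but blinded adjudication and the strict condition for a rating of not related leave room for an occasional grade.
- **The DSMB could not interpret an SAE excess.** Table 1 reports hospitalizations, ED visits, falls with injury, medication errors with harm and deaths individually as well as in a composite. The SAE definition names life-threatening events as a criterion of their own. The DSMB receives unblinded data and includes emergency and hospital medicine expertise. It can see what kinds of event make up an excess. What it lacks is a comparable grade within a kind of event.
- **Judging relatedness first breaks the blinding.** Any unmasking comes from access to the health record, which section {17a} discloses. Recording severity first is a sensible precaution against the relatedness judgement colouring the grade, and no more than that.
- **A count of ungraded events shows the harm.** The article gives no SAE rate for usual care. Any count would be an assumed rate times the 120 planned per group, and it would not measure harm.

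It can also be said that the severity scale is coarse: its top category could fit many ED visits and admissions. That limits what the grades can add, but the article chose this scale and plans to use it.

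**Conclusion.** The point holds in a limited form. As written, severity is graded for events judged related to the intervention. Usual-care events will therefore rarely be graded, and intervention-arm events judged not related will not be. The severity data are a selected subset and cannot support a comparison between arms.

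Its size is small and cannot be put as a number from the document. The primary outcome, the Table 1 safety outcomes and the pause trigger are untouched. The conclusion rests on two things: that the severity sentence means what it says, and that usual-care participants receive no paramedic care during the 30 days, as planned. It is a cheap improvement to safety monitoring, not an error that threatens the trial's main result.

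**What to change.** Change the severity sentence in section {22} so that:

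- every adverse event in both arms receives a severity grade at the committee review that already assesses relatedness;
- the grade is recorded before relatedness is judged, by the same procedure in both arms;
- any severity-by-arm table shown to the DSMB uses this grade.

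Duplicate review of related events may continue, but its severity result should not feed the between-arm table. Otherwise related events, which arise almost entirely in the intervention arm, would be graded twice and usual-care events once, and ascertainment would again differ by arm.

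The cost is one extra field per event and slightly longer adjudication. The committee already sees every event, so no new data collection is needed.

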#### Intervention description {11a}

The CACP program is an extension of an established care delivery model offered by the Mayo Clinic Ambulance Service. In the CACP program, the referring clinician identifies services or interventions clinically required for the patient. This may include patient education, clinical reassessment, laboratory specimen collection, medication administration, wound care, and other services within the CP scope of service. Visits are limited to up to two per day and are generally no more than 2 h in duration. The referring service or the patient’s primary care provider (PCP) or another ambulatory care provider, as appropriate, oversees clinical care with the support of the CP medical director. CPs will communicate with the referring service and/or their medical director as appropriate (usually after every visit but individualized based on the patient’s need and instructions provided by the referring service) via EHR inbox messages, the EHR chat function, or telephone. Patients will graduate from the program once the goals outlined in the referral are completed. Upon graduation, the CP team will communicate directly with a clinician assuming the patient’s care (e.g., PCP).

The CACP program will be available to patients at no cost, and services provided by CPs under this trial will not be submitted to participating patients’ insurance. If CPs facilitate or assist with a service performed by other members of the health care system, the services performed by others will be processed by the patient’s insurance as per usual procedures. For example, if a patient is seen for clinical assessment, venipuncture with laboratory sample collection, and administration of intravenous fluids, the assessment, venipuncture, IV start, and IV fluids themselves will be free to the patient. However, the analysis of the blood sample conducted by a clinical laboratory after it is collected and delivered by CPs will be processed through insurance. In contrast, point-of-care testing performed by CPs will be at no cost to the patient.

Participants randomized to usual care will be treated without consideration of CP care options. We anticipate that most will be referred to the ED and admitted to the hospital or have alternative care pathways (e.g., home health agency, SNF, frequent clinic visits) to meet their clinical needs. The start time for both cohorts will be the day after randomization.

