#### Participant timeline {13}

The schedule of enrollment, intervention, and assessment for patient participants is shown in Table 3. Adults (age ≥ 18 years) being treated in the pre-hospital environment (e.g., outpatient clinic or home), ED, or hospital will be identified by their treating clinicians as needing and being clinically appropriate for outpatient management with supportive services provided by the CP team. Clinicians will query patient interest, and a member of the study team will subsequently approach, consent, and enroll patients. Subsequent to consent, they will be randomized 1:1 to CACP versus continued usual care, with stratification by source of referral (pre-hospital versus ED versus hospital) and location (Minnesota versus Wisconsin, corresponding to the two different CP teams delivering the intervention). Participants randomized to CACP will be eligible to receive CP services as ordered by the referring clinician. Participants randomized to usual care will continue to receive care as they would otherwise, including being referred to the ED (for patients in the pre-hospital setting), admitted to the hospital (for patients in the ED), or remain in the hospital (for patients already in the hospital) as appropriate.

**Table 3 Tab3:** Flow of study procedures for patient participants

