Throughout the course of the study, we will also monitor AEs in both study arms and may suspend accrual if patients are experiencing a large number of adverse events. In particular, we will temporarily suspend accrual if, at any time, observed events meet the following criteria: (1) If, within the first 30 patients, 2 or more patients in the CACP arm than the usual arm experience a SAE, the study will be paused for review by the DSMB; (2) if, after the first 30 patients, the proportion of participants in the CACP arm who experience an SAE is ≥ 10% greater than the proportion of participants experiencing SAE in the usual care arm, the study will be paused for review by the DSMB.

If unexpected adverse event profiles are observed which do not meet the above criteria, but are worrisome, we may still consider temporarily suspending accrual. Adverse event-stopping rules may be modified if, during the study, new information becomes available, which suggests that such a modification is necessary, or, if after temporarily stopping accrual, the above rule is found to be overly conservative.

Reports containing efficacy, AE, and administrative information will be compiled and presented to the DSMB every three months.

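### The SAE pause rule can count the usual-care pathway as usual-care harm, and the scale of its 10% margin is not stated

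*Protocol article*

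**What the plan says.** All from the protocol article.

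- **SAE definition** (Adverse event reporting and harms {22}): besides death and life-threatening events, SAEs include events that "result in an ED visit or hospitalization, or cause persistent or significant disability or incapacity". The list of monitored events reads: "The study team will monitor for AE in both groups including ED visits, unplanned hospitalizations, deaths, falls with injury, and medication errors".
- **Pause rule** (same section): accrual is suspended if "at any time, observed events meet the following criteria". The first criterion is that "within the first 30 patients, 2 or more patients in the CACP arm than the usual arm experience a SAE". The second, after 30 patients, is that "the proportion of participants in the CACP arm who experience an SAE is ≥ 10% greater than the proportion of participants experiencing SAE" in the usual-care arm. Either one leads to a pause for DSMB review. The statistician checks ED visits, hospitalizations and deaths weekly.
- **Expected usual care** (Intervention description {11a}): "We anticipate that most will be referred to the ED and admitted to the hospital or have alternative care pathways". Participant timeline {13} describes usual care by source of referral, "including being referred to the ED (for patients in the pre-hospital setting), admitted to the hospital (for patients in the ED"; patients already in hospital stay there.
- **Safety comparison** (Table 1): unplanned hospitalizations, ED visits, injurious falls, harmful medication errors and death, reported as a composite and singly.

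The harms section does not set aside the ED visit or admission through which usual care is delivered. It also gives no expected SAE rate, no time window for events counted by the rule, and no scale for the 10%.

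**The concern.** The rule treats the usual-care SAE proportion as the background against which harm from CACP would show. For patients referred from the pre-hospital or ED setting, part of that proportion can be the very ED visit or admission the program is meant to replace. Counting it raises the comparator, so CACP must exceed a raised rate by the margin before the trigger fires. The ED-visit and hospitalization components of the Table 1 safety comparison, and the composite containing them, are exposed in the same way.

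The word unplanned does not resolve this. The protocol excludes only admissions for scheduled surgery, procedures or treatment, and an ED referral or an admission from the ED is neither.

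The second problem is the margin itself. If usual care is at 20%, a 10% excess means 30% on the absolute reading and 22% on the relative one. Two people applying the rule in good faith could disagree on whether accrual must pause. At stake is whether the one numeric safety trigger, in a trial that moves acute care into the home, responds to harm and can be applied reproducibly.

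**Working it through.** The plan states no operating characteristic for the rule, so there is no figure of its own to reproduce. The check asks how the rule as written behaves.

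**Inputs from the protocol**
- 120 patients per group, so 240 in total, allocated 1:1.
- Criterion 1 through patient 30: CACP minus usual care ≥ 2 patients with an SAE. Criterion 2 from patient 31: the 10% margin.
- Checks at any time (after every patient) or weekly. Recruitment from January 21 to December 31, 2022 is about 49 weeks, and 240/49 ≈ 5 patients per week.

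**Assumptions (not in the protocol)**
- The SAE rates.
- The share e of usual-care patients with an index encounter counted.
- Blocks of 4, and SAE status known at once.
- 20,000 simulated trials per setting.

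**Step 1: shift in the comparison.** Let the true non-index SAE rates be 35% (CACP) and 20% (usual care), a true excess of 15 points. With index encounters counted, the usual-care rate becomes 0.20 + 0.80e. The top value of e is one third of patients pre-hospital × 70% sent to the ED ≈ 0.23.

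| e | Usual-care rate | Apparent excess | Pause probability, every patient | About weekly |
|---|---|---|---|---|
| 0 | 0.200 | 15.0 points | 0.97 | 0.96 |
| 0.05 | 0.240 | 11.0 | 0.92 | 0.90 |
| 0.10 | 0.280 | 7.0 | 0.83 | 0.80 |
| 0.15 | 0.320 | 3.0 | 0.73 | 0.67 |
| 0.23 | 0.384 | −3.4 | 0.56 | 0.48 |

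Both criteria are applied and the margin is read as absolute. The expected difference drops below 10 points once 0.35 − (0.20 + 0.80e) < 0.10, that is e > 0.05/0.80 = 0.0625. Beyond that, any pause depends on early small numbers and sampling variation.

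**Step 2: the two readings of 10%.** At 120 per arm with 24 usual-care patients having an SAE (20%), the absolute reading needs a CACP proportion of 0.30, or 36 patients. The relative reading needs 1.10 × 24 = 26.4, so 27 patients. The excess required is 12 patients or 3.

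The probability of at least one pause when the true rates are equal (both criteria, every patient) is:

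| Equal SAE rate | Absolute | Relative |
|---|---|---|
| 5% | 0.19 | about 0.76 |
| 10% | 0.36 | about 0.80 |
| 20% | 0.54 | about 0.81 |
| 30% | 0.61 | about 0.81 |
| 40% | 0.66 | about 0.80 |

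**Step 3: do both effects apply at once?** With usual care 20 points higher (20% v 40%, or 30% v 50%), the pause probability on the absolute reading and every-patient checking is about 0.15 to 0.22. The equal-rate figures in Step 2 therefore do not carry over to a trial in which usual care has a large SAE excess.

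Repeat runs agree to within about 0.01 to 0.02.

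**The case against.** The case for leaving the rule alone has several parts, and some of it stands.

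- **Counting window.** Follow-up in both arms starts the day after randomization, and a Table 1 safety time point uses that start. An ED visit on the day of randomization may fall outside it. This limits e, but the harms section does not say that the pause rule uses this window.
- **Who is affected.** Hospital-referred patients who remain have no new admission, ED-referred patients are already in the ED, and alternative pathways are foreseen. So e may be small, and at 5% the rule still pauses with probability 0.92. This stands, and it is why a range is shown.
- **Other safeguards.** Accrual may be suspended at discretion, the DSMB sees unblinded results every three months, AEs are adjudicated for relatedness, and deaths, falls and medication errors are reported separately. A reader might infer that the rule hides harm outright. The documents do not support that. However, none of these safeguards corrects the numeric trigger, which counts SAEs whether or not they are related.
- **Chance pauses.** A reader might infer that the trial will more likely than not be paused by chance. On the absolute reading that needs equal SAE rates of about 20% or more with frequent checks, and the protocol states no rate. Nor can it be joined to the masking argument (Step 3). A sensitive trigger without formal error control is a legitimate safety choice. It leads to a pause, not termination, and the protocol allows the rule to be modified.

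**Conclusion.** The point holds in a limited form. As written, the SAE definition, the expected usual-care pathway and the between-arm pause rule do not fit together: encounters that are usual care can count as usual-care SAEs, which biases the numeric trigger against detecting harm from CACP. The size depends on an SAE rate and an index-encounter share that the protocol does not give. In the illustration, a true 15-point excess is flagged with probability 0.92 to 0.56 as the share goes from 5% to 23%, against 0.97 with none (0.90 to 0.48 against 0.96 with about weekly checks). The effect is a loss of sensitivity in one safeguard among several.

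Independently of any assumed rate, the 10% margin has two readings that lead to very different behaviour, so the criterion is not fixed well enough to apply. These are matters to put right, but they do not threaten the primary analysis.

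**What to change.** - Reconcile the SAE definition in Adverse event reporting and harms with the usual-care pathway in Intervention description and Participant timeline. The existing adjudication committee would flag, by one definition in both arms, the ED visit or admission that directly continues the index referral.
- Tabulate flagged encounters separately. In the pause rule and the Table 1 safety comparison, compare deaths and all other SAEs without them, and show the all-SAE comparison alongside.
- State the time window for events counted by the rule.
- State whether 10% is absolute or relative.
- Give the DSMB the rule's simulated operating characteristics at the stated checking frequency, over a range of SAE rates.

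Keep the at-any-time and weekly monitoring: reducing it to the three-monthly DSMB meetings would delay detection. Decisions on pausing and resuming stay with the DSMB.

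The cost is one yes/no field for a committee that already reviews these events, a few sentences of text and a short simulation. The downside is some judgement in labelling index encounters; showing the all-SAE comparison as well keeps that judgement visible.
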